Between 1998 and 2003 our research team carried out a cohort study of patients with COPD in two health centers in Malaga. The Batalla Test [19], the Morinsky-Green test [20] and the self-reported compliance from Haynes and Sackett test [21] were all included as treatment adherence evaluation methods. We found little consistent data. Between 2004 and 2006, we performed another cohort study in 195 COPD patients from 4 health centers. Patients have been followed up during 1 year and we have used four therapeutic adherence measures: the Batalla test, the Morinsky-Green test, the Haynes-Sackett test and the dose/pill count. In this study we selected the dose/pill count as the reference method to measure adherence and we calculated the diagnostic validity of the self-reported methods. We found that the use of the Batalla test and the Morisky-Green test together was the most reliable way to assess adherence by self-reported methods and we proposed a strategy to measure adherence in clinical practice depending on the adherence prevalence [22]. Taking all this into account, our next step in the study of adherence was the design of a multifactor intervention to improve treatment adherence in patients with COPD.

The main objective of this study is to evaluate the effectiveness of a multifactor intervention (COPD information, dose reminders, audiovisual material, motivational aspects and inhalation techniques training) to improve the therapeutic adherence in COPD patients with inhaled scheduled treatment after one year follow-up with two reinforcement visits (3 and 6 month after intervention). The second objective is to describe the main factors related to adherence. The specific aims are:

- To evaluate in two study groups treatment adherence prevalence with inhaled medication (primary outcome variable) at the beginning of the study, at three and six months and at one year after the intervention.

- To evaluate the functional status using a forced spirometry and the quality of life (St George Respiratory questionnarie, EuroQoL-5D) and the clinical progress (SeguiEPOC) as secondary outcome measures in both groups.

- To analyse the main factors related to therapeutic adherence.

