### Recruitment

Patients will be contacted using their health center records. They will be invited to participate in the study after a brief explanation by telephone about the research aims and they will receive an appointment in the health center. At this first appointment (inclusion visit) patients will receive more detailed information about the study and if they agree to participate, they will sign the written consent.

At this point, subjects will be divided randomly into two groups using the block randomization technique. The blocks consist of 4 patients, two subjects per group [Intervention (I) and control (C)]: (IICC); (CCII); (CICI); (ICIC); (ICCI); (CIIC). Consequently, the numbers in the two groups never differ at any time by more than two. The blocks will be marked with a number from 1 to 6 and we will choose blocks at random to create the allocation sequence using a sequence of random numbers generated by Microsoft Excel 2003 program with the function fx:RAND(). We will need 35 random blocks; and the final list of the included patients in each arm of the trial will be set in advance. The researcher who will allocate the patient will have the open-list of randomization, but there will be no change of patient group related with the subjects characteristics. Because the patients are from 6 health centers, the randomization and the presence of the intervention and control subjects in all the health centers will be guaranteed.

After randomization all the study data will be recorded and the adherence will be measured in both groups.

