### Follow up

#### Control Group

they will be appointed for:

Visit 1: It will take place 3 months after the inclusion. It will involve the measure of adherence and other variable changes.

Visit 2: It will take place 6 months after the inclusion. It will involve the measure of adherence and other variable changes.

Visit 3: It will take place after 1 year follow up. All the study data will be recorded including treatment adherence.

There will be a pre-adherence visit before each follow-up visit except for the inclusion one. The reason for the pre-adherence visit is to ask the patient to bring a new container that will be marked with the date in which it is opened in order to count doses/pills through the month. This is done because most of the devices that patients use last 30 days. The pre-adherence visit will be done by telephone to guarantee the follow-up.

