#### Intervention Group

After the inclusion, the first part of the intervention (group session) will be carried out in each health center and the intervention group will receive appointments for:

Visit 1: It will take place 3 months after the intervention. It will involve the measure of adherence and other variable changes, encouragement about inhalation techniques and motivational aspects related to treatment adherence.

Visit 2: It will take place 6 months after the intervention. It will involve the measure of adherence, other variable changes and encouragement about inhalation techniques and motivational aspects related to treatment adherence.

Visit 3: It will take place after 1 year follow-up. All the study data will be recorded and encouragement about inhalation techniques and motivational aspects related to treatment adherence.

There was a pre-adherence visit prior to all visits as explained previously.

Adherence will be measured at each visit to control its evolution during the follow-up period. All individual follow-up visits will be videotaped to identify the motivational aspects and skills which each patient needs to be applied at the next visit.

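### Baseline measures are recorded after open-list randomization, and no baseline procedure is described for the reference dose count

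*Protocol article*

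**What the plan says.** The Recruitment section gives the order of events at the inclusion visit. The patient signs consent, and then: "At this point, subjects will be divided randomly into two groups using the block randomization technique". On access to the sequence it says: "The researcher who will allocate the patient will have the open-list of randomization". Measurement follows allocation: "After randomization all the study data will be recorded and the adherence will be measured in both groups".

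The first specific aim, at the end of the Background, is: "To evaluate in two study groups treatment adherence prevalence with inhaled medication (primary outcome variable) at the beginning of the study". The full set of times is "at the beginning of the study, at three and six months and at one year after the intervention". The Primary outcome section names three adherence measures, the Morisky-Green test, the Batalla test and the dose/pill count. It makes the count the reference and treats each measure independently.

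The count depends on a preparatory telephone contact at which the patient is asked for a new container, to be "marked with the date in which it is opened in order to count doses/pills through the month". The Control Group section limits that contact: "There will be a pre-adherence visit before each follow-up visit except for the inclusion one". The Intervention Group section adds: "There was a pre-adherence visit prior to all visits as explained previously".

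**The concern.** Two separate weaknesses affect the starting values.

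The first is order. A baseline value is protected from the allocation only if it is fixed before anyone involved can know the arm. Here the arm is assigned first, from a readable list, and the article describes no masking of patients or of those who record data. Questionnaire answers can then shift with knowledge of the arm, through the patient's expectations or through the way questions are put and scored. An imbalance that arises this way would look like chance imbalance at baseline, and adjusting for it could introduce bias.

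The second is the reference measure. If the count has no proper starting value, the trial cannot show on its preferred measure that the arms began alike, and the planned description of how adherence evolves has no comparable first point for that measure.

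**Working it through.** The document gives no figure for this point, so the check sets the passages side by side.

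**Step 1: order of events at inclusion (Recruitment).**
1. Written consent.
2. Allocation, in blocks of 4. The plan's 35 blocks × 4 = 140, so the order applies to every patient.
3. Recording of all study data and adherence.

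The article states this order outright. It is not a gap left for another document to fill.

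**Step 2: which baseline items are exposed (Outcomes; Independent variables).**
- Patient-reported and clearly exposed: Morisky-Green, Batalla, the St George questionnaire, EuroQoL-5D, and the family and social support scales.
- Much less exposed: spirometry and prescribed medication.
- Hardly exposed: age and sex.

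**Step 3: where the exposed items enter the analysis (Statistical Analysis).**
- Primary outcome: a between-group chi-square test with no baseline term. There is no direct effect.
- Logistic model: intervention plus the listed independent variables as possible modifying factors. Family and social support are on that list, so covariates measured after allocation enter here. Baseline adherence is not on the list.
- Secondary outcomes: analysis of variance, not stated to be on change scores. There is an effect only if change from baseline is analysed.
- Baseline comparison of the arms: affected.

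**Step 4: adherence measures against time points.** Three measures at four times give 3 × 4 = 12 combinations.

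| Measure | Inclusion | 3 months | 6 months | 1 year |
|---|---|---|---|---|
| Morisky-Green | questionnaire, no window needed | yes | yes | yes |
| Batalla | questionnaire, no window needed | yes | yes | yes |
| Dose/pill count (reference) | **no window described** | dated container | dated container | dated container |

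The article describes a workable procedure for 11 of the 12. The one without is the reference measure at baseline.

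**Step 5: can another passage supply the missing window?**
- The sentence in the Intervention Group section points back to the rule already given, which exempts inclusion. It does not restore a baseline contact.
- The recruitment telephone call covers the research aims and an appointment. No container is mentioned.
- A container opened at the inclusion visit would be counted over a month after randomization. The group session follows inclusion with no minimum delay stated, so in the intervention arm that month could overlap the intervention.

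**The case against.** The strongest reply is that the randomized comparison does not need baseline values. The primary test is a chi-square between groups, and neither biased nor absent baseline adherence distorts it directly. That is correct, and it limits how serious the point is.

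The conflict with the first aim can also be read more mildly. The aim asks for adherence at the start without naming the dose count, and the two questionnaires can supply it because each method stands on its own. This stands in part. The aim can be met on the questionnaires, but the article does not say so, and the count remains its reference method.

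The Study limitations section mentions a researchers' manual setting out what to measure at each visit. It is not shown and may describe how a count is made at inclusion. That is possible, so the supported statement is that no baseline counting procedure is described. A reader might infer that the baseline count will be missing in every patient, but the text says only that adherence is measured in both groups at that point, without saying how the count is done or that it is omitted.

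Two further inferences are tempting and not supported. One is that the holder of the list also records the baseline data: the article says who allocates, not who measures. The other is that patients already know their arm when they answer: no passage says when they are told. The concern rests on the stated order together with the absence of any described masking. The assurance in the Recruitment section that patients will not change group because of their characteristics concerns allocation and does not protect the measurements that follow it.

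Finally, the group session comes after inclusion, so the inclusion questionnaires appear to precede any intervention. That removes contamination by the intervention itself, but not the influence of knowing the arm.

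**Conclusion.** The point holds with limited reach. Recording patient-reported baselines after open-list allocation leaves them avoidably exposed in all 140 patients. The consequences fall on the baseline comparison, on any change-from-baseline analysis and on the self-reported covariates in the logistic model. The direction and size of any bias cannot be derived from the document. A reader might infer that the primary result is biased, but the planned chi-square test uses no baseline value, so the document does not support that.

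On the reference measure, the only counting procedure described excludes the inclusion visit. A baseline count comparable with those at 3, 6 and 12 months is therefore not provided for, while the first aim includes adherence at the start. This is a gap between aim and procedure, not proof that the data will be absent.

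The conclusion assumes that no masking of baseline recording exists beyond what the article describes, and that the unseen manual does not set a different order or a separate baseline count. It should be fixed before enrolment, because baselines taken in the wrong order cannot be recovered. It is not a reason to reject the design.

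**What to change.** 1. Reorder the inclusion visit: consent, then all baseline measurements, then reveal of the allocation. It is the same visit with the same measurements, so it adds no cost.

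2. Restate the first aim so that baseline adherence rests on the Morisky-Green and Batalla tests, with the dose/pill count starting at Visit 1. This costs one sentence and gives up any claim to a baseline on the reference measure.

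3. The alternative to item 2 is to complete a dated count before allocation. That would give a comparable baseline, but it takes about a month and a further contact, separates consent from randomization and allows losses in between. It also means observing dose-taking beforehand, which bears on the Hawthorne effect discussed under Study limitations. It is a trade-off for the investigators to weigh. Item 1 is worth doing either way.

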### Follow up

#### Control Group

they will be appointed for:

Visit 1: It will take place 3 months after the inclusion. It will involve the measure of adherence and other variable changes.

Visit 2: It will take place 6 months after the inclusion. It will involve the measure of adherence and other variable changes.

Visit 3: It will take place after 1 year follow up. All the study data will be recorded including treatment adherence.

There will be a pre-adherence visit before each follow-up visit except for the inclusion one. The reason for the pre-adherence visit is to ask the patient to bring a new container that will be marked with the date in which it is opened in order to count doses/pills through the month. This is done because most of the devices that patients use last 30 days. The pre-adherence visit will be done by telephone to guarantee the follow-up.

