### Outcomes

#### Primary outcome

the therapeutic adherence considered as the percentage of patients classified as good adherent. The adherence will be measure by three adherence measurements: the Morinsky-Green test (MGT) [20], the Batalla test (BT) [19] and the dose/pills count. We will consider as reference methods the results of dose/pill count. Each method will be considered independently.

The MGT measures the attitude towards treatment and it was adapted by us to inhaled medication. The test has four questions and a patient will be considered a good adherent when he answers properly the complete questionnaire.

The BT provides information about the patients' knowledge of their illness. The test has three questions, adapted to COPD, and a patient will be considered a good adherent when he answers properly the complete questionnaire.

The dose/pill count is the number of pills or doses taken divided by the number of pills or doses prescribed, multiplied by 100 (expressed as a percentage). According with Sackett et al. [21] recommendations, a good adherence is considered when the result of counting is between 80% (a twenty percent of doses/pills missed) and 110% (the patient inhales a ten percent more of doses/pills) of dose/pill prescribed. This cutoff point was selected for consistency with other studies [24-26].

We consider the dose/pill count as the more confident method. We use the two self-reported methods because they are easier to apply in clinical practice and, in a previous work conducted by us, we found acceptable indicators of their validity as diagnostic test for treatment adherence in COPD patients under certain environment circumstances.

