### Study limitations

The main study limitation is the selection bias due to the missing data. In order to diminish this bias, we will apply several strategies:

- An increase of 15% in the sample size (expected losses)

- Three phone calls at different days and times for unreachable patients

- Rescue appointments for the non-assistants to visits (three different appointments)

Other aspect is the Hawthorne effect along the study (ie, tendency of subjects participating in a research study to change their behaviour). Although this could affect overall estimates the adherence, the implications might be less important in comparing results of different measurements tools (unless, of course, the effect is differentially captured by each measurement tool); furthermore, it is difficult to perceive that any potential Hawthorne effect would be maintained over the many months of study.

In addition we take into account the possible contamination between the control and the intervention group because of the relationship between subjects in their daily life (neighborhood, relatives, social networks or associations). However, in another educational intervention study performed with obese patients in our area we did not find a significant level of this effect [35]. We also believe that the intervention characteristics (several steps, small groups and individual visits) that we have described will have little influence on contamination between groups.

Another important aspect to consider is the protocol and the intervention standardization. This is why the dynamic has been structured in an exhaustive way and the intervention will be performed by two professionals trained in communication, disease knowledge and inhalation techniques of the different devices used by COPD patients. Furthermore, we have designed a manual for the researchers where we explain the working plan, the different parts of intervention (the group session and the individual visits), the protocol scheme to know what they have to measure each time and the details to asses each variable included in the study. In this way, the procedure can be replicated elsewhere.

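### For devices holding 30 days of doses, one marked container counted over about a month cannot show use above 110%, so over-users are classed as good adherent on the reference measure

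*Protocol article*

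**What the plan says.** Under Primary outcome, the protocol article measures adherence in three ways and gives one of them priority: "We will consider as reference methods the results of dose/pill count". The count is "the number of pills or doses taken divided by the number of pills or doses prescribed, multiplied by 100". It is then dichotomised with a lower and an upper limit: "a good adherence is considered when the result of counting is between 80% (a twenty percent of doses/pills missed) and 110" per cent of the prescribed amount. Taking too much is thus meant to fail the definition, as taking too little does.

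Under Follow up, Control Group, each of the three follow-up visits is preceded by a telephone contact, at which patients are told to "bring a new container that will be marked with the date in which it is opened". This step is taken "in order to count doses/pills through the month", and the reason given is that "most of the devices that patients use last 30 days". The Intervention Group section applies the same procedure to the other arm.

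Under Study limitations, the plan offers "Rescue appointments for the non-assistants to visits (three different appointments"), without saying when these take place. The same section mentions a manual for the researchers that covers how each variable is assessed. It is not part of the published article.

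**The concern.** The definition of good adherence has an upper limit, but the procedure that supplies the data has a ceiling of its own. A single container cannot show more doses taken than it holds. If it holds about a month of prescribed doses and is counted after about a month, the result stops near 100% however much the patient used. A patient who empties it early and continues from an unmarked container looks like one who took exactly what was prescribed.

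The affected measure is the reference method of the primary outcome, at every follow-up visit. The intervention aims to raise use, so a patient who moved from under-use to over-use would be recorded as improved, although the plan's own definition says otherwise. Doses taken from a container that nobody counted cannot be recovered at the analysis stage.

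The same ceiling makes the result depend on the day of the count, and the article fixes neither that day nor the period over which prescribed doses are summed.

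**Working it through.** **Inputs.** The limits of 80% and 110% and the ratio of doses taken to doses prescribed come from Primary outcome. The single marked container, the month-long window and the 30-day capacity of most devices come from Follow up, Control Group. The plan gives no figure of its own for this point; its one computed design figure, the total of 140 patients, does not enter the argument.

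**Notation.** T is the number of days from opening to the count, and u is true use as a fraction of prescribed. The container holds 30 days of prescribed doses and only that container is counted. Doses recorded as taken, in days' worth, are min(u × T, 30).

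**Denominator to the count date.** Measured adherence is min(u × T, 30)/T, so its ceiling is 30/T.

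| Day of count | Ceiling | Measured at u = 100% | Measured at u = 120% | Measured at u = 150% |
|---|---|---|---|---|
| 24 | 125.0% | 100.0% | 120.0% | 125.0% |
| 27 | 111.1% | 100.0% | 111.1% | 111.1% |
| 28 | 107.1% | 100.0% | 107.1% | 107.1% |
| 30 | 100.0% | 100.0% | 100.0% | 100.0% |
| 31 | 96.8% | 96.8% | 96.8% | 96.8% |
| 35 | 85.7% | 85.7% | 85.7% | 85.7% |
| 38 | 78.9% | 78.9% | 78.9% | 78.9% |

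- A result above 110% needs 30/T > 1.10, so T < 30/1.10 = 27.3 days. No count at 28 to 31 days can cross the limit.
- At u = 150% the container is empty on day 30/1.5 = 20, and at u = 120% on day 30/1.2 = 25. Both read 100% at day 30.
- A fully adherent patient falls below 80% only if 30/T < 0.80, so T > 30/0.80 = 37.5 days. At days 31 to 37 the result is 96.8% to 81.1%, still good adherence.

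**Denominator fixed at 30 days.** Measured adherence is min(u × T, 30)/30.

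- The ceiling is 100% whatever the day, so the upper limit never operates.
- A late count now flatters under-users: u = 70% at day 35 gives 0.70 × 35/30 = 81.7%, which passes.
- An early count penalises full adherence: u = 100% at day 20 gives 20/30 = 66.7%, which fails.

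**Longer-lasting devices.** A container holding 60 days of doses has a ceiling of 60/30 = 200% at day 30, so over-use can be seen.

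**The case against.** Three arguments on the other side carry weight.

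First, the article says most devices last 30 days, not all. Longer-lasting containers escape the ceiling, and so does a count before day 27.3. This stands and limits the scope. It does not remove the point, because the month-long window is justified by the 30-day devices themselves.

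Second, the interval to the count, the visit tolerance and the handling of replacement containers may be in the researchers' manual, and an article need not print them. This also stands for those details, and their absence is not the finding. The finding is that what the article does state (an upper limit of 110%, one marked container, 30 days of contents, a month of counting) does not fit together.

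Third, the article gives no rate of over-use, and its Background describes the problem mainly as patients failing to take treatment. The number misclassified is therefore unknown and could be small. The two questionnaire measures are unaffected, although they are not the reference.

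A reader might go further and infer that any late visit makes a fully adherent patient non-adherent. The document does not support this. It would take a count after day 37.5, a denominator running to the visit and no replacement container counted. The article states none of the three, and with a fixed 30-day denominator a late count errs the other way. The offer of rescue appointments makes delayed counts conceivable, but no timing is given and nothing says that the old container is reused.

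A reader might also infer bias between arms through different punctuality. The procedure is the same in both arms and the document gives no attendance rates, so any such figure would only restate an assumption.

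**Conclusion.** The point holds in a limited form. For devices holding 30 days of prescribed doses, a count of one marked container at 28 to 31 days cannot exceed 107.1% to 96.8%. The 110% limit is then inoperative, and true use of 120% or 150% is classed as good adherence on the reference primary measure. This rests on two readings of the article: that only the marked container is counted, and that the count falls about a month after opening.

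Dependence on timing is a second, conditional consequence. Its direction turns on the unstated denominator: full adherence is lost only after day 37.5 if the denominator runs to the visit, while late counts inflate under-users if it is fixed at 30 days. The effect on the trial's result cannot be sized from the document.

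**What to change.** - Time the existing pre-adherence call so that the count falls before about day 27 of a 30-day container, for example at day 20 to 25. The ceiling is then 30/25 = 120% to 30/20 = 150%, so use above 110% is classed correctly even if the container is already empty.
- Ask patients to bring every container of that drug used since the marked date, and count them all.
- Define the denominator as the doses prescribed from the marked date to the date of the count. The earlier count needs this rule: against a fixed 30 days, a fully adherent patient would read 66.7% at day 20.
- For a rescue appointment, repeat the call and mark a new container, so that the window is of similar length for all patients in both arms.

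The denominator should not be ended at the day the container ran out. The plan records no such date, and the rule would hide patients who finished the container and then stopped.

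The cost is a change in the timing and wording of a call already planned, and an entry in the researchers' manual. The counting window becomes slightly shorter, so each missed dose weighs a little more, and some calls will have to be repeated.
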